#### Exclusion criteria

- contralateral limb or upper limb amputation that would interfere with completion of study activities
- are unable to use more than one of the test feet for any reason (e.g., excessively long residual limb that is not compatible with wearing study prosthetic feet)
- unable to walk under the minimal necessary study walking conditions in order to complete the study procedures without undue stress
- current surgical, neurological, rheumatologic, or lower limb musculoskeletal problem that significantly impairs ambulation (e.g., current ulcer, terminal illness)
- weight greater than 263lbs.
- inadequate cognitive or language function to consent to participate
- currently incarcerated
- impaired decision-making ability or the use of a legally authorized representative

## **2.5 Study Evaluations**

### **Data Collection**

There is an overview of the data collection presented in Figure 1. The methods are then described in detailed below. Study staff will be trained to carry out all of the protocol, including biomechanical gait data collection, and using the treadmills, the commercial prosthetic feet and PFE. This training may include onsite instruction and testing with equipment vendors and suppliers, as needed.

[figure not shown]

**Figure 1.** Schematic diagram of data collection study visits and outcome measures.

### Visit 1: Screening, Prosthetic Foot Emulator Fitting, and Assessment Visit (approximately 3 hours)

After consent, participants will be assessed to determine if they can safely and successfully use the necessary study commercial prosthetic feet and the prosthetic foot emulator. For example, if a participant's residual limb length is too long to accommodate more than one of the prosthetic feet or if any other residual limb condition that precludes use of a prosthesis (e.g., ulcer) is present, she/he will be withdrawn from the study. Individuals who are determined to be not eligible will be compensated \$50 for their effort.

Eligible participants will be asked to fill out the baseline self-report surveys; we will explain that they do not have to answer any questions they do not want to.

Participants will then be asked to complete a walking test called the Two-Minute Walk Test (2MWT) using their own prosthesis. They will be asked to walk continuously back and forth between two cones on level ground for 2 minutes; however, they may stop or take a seated rest break at any point during the test. Participants will be instructed to walk as quickly and safely as they can during this test. Study staff will walk alongside the participants to ensure safety during the test. Participants may use an assistive device, such as a cane or walker, when performing this test. We will record the total distance participants walked during the test.

In order to further assess the effect of the prosthetic foot type on balance and stability in people with LLA, we will conduct a set of baseline performance-based outcome measures (detailed below), in the following order, using their prescribed prosthesis. Participants will be encouraged to take as many rest breaks as needed throughout testing.

1. Berg Balance Scale (BBS): The BBS is a 14-task performance-based measure designed to assess static balance and fall risk in clinical populations. Each task is scored between 0-4, determined by ability to perform the assessed activity. These task scores are then summed to produce a final score. The BBS takes 10-20 minutes to complete. All tasks will be done while the participant is wearing their prescribed prosthetic foot.
2. The Four-Square Step Test (FSST): The FSST is a clinical outcome measure designed to assess dynamic balance. Participants are asked to step quickly in a 4-step pattern (i.e., forward, laterally, and backward) over canes (e.g., PVC piping) laid on the floor as per standard administration of the test. Participants complete the test twice while wearing their prescribed prosthetic foot, and the fastest of the two times required to complete the test is recorded. The FSST, including instructions, a practice trial, and the two timed trials, takes no more than 5 minutes to complete.
3. 4 Stage Balance Test (4SBT): The 4SBT is a performance-based test of static balance. There are up to four standing positions that get progressively more challenging to maintain for 10 seconds without moving their feet or needing support. The four positions are: feet side-by-side, placing instep of one shoe so it is touching the big toe of the other shoe; tandem stance of one shoe in front of the other with heel touching toe; and standing on one foot. Each position is described and demonstrated to the participant. Then, the participant may be guided and supported into assuming each correct position. When the participant is steady, they are timed to see how long they can maintain the position, but with close guarding ready to assist them if they should lose their balance and need to take a step. If the participant can hold a position for 10 seconds without moving their feet or needing support, they proceed to the next position. Participants are scored based on how many of the four stages they can safely complete.
4. Narrowing Beam Walking Test (NBWT): The NBWT is a performance-based test of balance for lower limb prosthesis users. It is comprised of four sets of low-to-the ground (i.e., approximately 4cm) beams that become increasingly narrow in width. Two practice trials and then three measured trials are performed with the distance walked on the beam averaged to produce a final score. The NBWT takes 3-5 minutes to complete. All trials will be done while the participant is wearing their prescribed prosthetic foot.
5. The L Test of Functional Mobility (L Test): The L test is a clinical measure designed to assess functional mobility. Participants will be asked to rise from a chair, walk 3 meters, turn at ninety degrees, walk 4 more meters and turn around, walk 4 meters, turn ninety degrees,

and return to the chair, and to a seated position. Time to complete the task is recorded. The L test takes 1-2 minutes to complete. One practice trial and three timed trials will be performed and the average time will be used for analysis. All trials will be done while the participant is wearing their prescribed prosthetic foot.

Participants will be asked to walk on the treadmill (e.g., AC5000M medical treadmill, SciFit, Tulsa, OK) with their prescribed prosthesis and to choose three walking speeds: comfortable, slow, and fast. Participants will choose these speeds by increasing and/or decreasing the speed on the treadmill. This will allow participants to practice walking on the treadmill before trying the study prosthetic feet. They will be allowed to hold onto the safety bars at any time on the treadmill if needed in order to keep their balance. They will also be offered the option of using additional supports (e.g., gait belt, overhead safety harness) while walking on the treadmill throughout the study.

Participants will be assigned to the low mobility group (LM) or the high mobility group (HM). LM vs. HM grouping will determine which 3 prosthetic foot conditions each participant will wear during the testing protocol. This grouping will be informed by the results of the participant's 2MWT test, based on a cut-off distance of 113 meters as a guideline with clinical judgement. Although 113 meters translates to 371 feet, we use a cut-off of >375 feet for logistical purposes (i.e., distance between cones that participants will walk between is 75 feet). This is to ensure that participants will be using prosthetic feet that would likely be considered for their respective mobility levels in the clinical setting. For example, if a participant's 2MWT test score is marginal, the study research prosthetist will use other clinical indicators (e.g., balance, fatigue, quality of walking) to help inform the group assignment to ensure the participant can safely and comfortably complete the study activities for their respective group.

**Please note:** All prosthetic fittings for this study will be completed by a certified prosthetist, and they will be performed to meet normal clinical care standards. The treadmills described in the procedures below are equipped with safety rails and emergency stop features; participants will be given the option of using additional supports (e.g., gait belt, overhead safety harness) during the walking tests on this equipment.

The study research prosthetist will fit participants with a robotic ankle-foot prosthesis (the multiaxial prosthetic foot emulator, PFE). The PFE will be attached to participants' current prosthetic socket in the same way that a regular prosthetic foot would be attached. The PFE can be programmed to operate in different modes that mimic the mechanical properties of different commercially available prosthetic feet. For this study, the PFE will be programmed with 5 foot modes – 3 high mobility feet and 3 low mobility feet (one foot mode is shared between high and low mobility groups). Designated research staff will use the computer software interface to switch the PFE between different foot modes and adjust hardware on the foot (e.g., adding small brass weights to mimic the weight of the corresponding prosthetic feet). Changing out the physical foot is not necessary. After participants are fitted with the PFE, we will give them time to

walk at their comfortable speed on the treadmill again while using the PFE in up to 3 different modes (3 high mobility vs. 3 low mobility modes depending on their 2MWT; see details above). Participants can choose to adjust their walking speed while walking with the PFE by increasing and/or decreasing the speed on the treadmill at any time. This will allow the participants to practice walking with the PFE and we will assess their walking ability to confirm whether the participant is a good fit for the study. Adjustments may be made to the PFE hardware or software settings in order to optimize the walking performance for each participant. If participants are not able to feel confident and stable on one or more of the modes, we will stop the session. We will also give participants time to rest at any point, and each time we switch foot modes. Participants may also be offered an opportunity to practice walking with the 3 different commercially available actual study feet.

At the end of the study visit, the prosthetist will refit the participants' prescribed prosthetic foot. The next study visit will be scheduled and a reminder slip can be given to the participant.

#### Visit 2: Randomization & First Initial Testing Visit – Emulator or Actual Feet (approximately 3 hours)

Based on the result of the 2MWT completed during Visit 1, participants have been assigned to the low mobility group (LM) or the high mobility group (HM) (see details above). At this visit, within each group (LM and HM) participants will be randomized to test either the PFE in the 3 foot modes for their group (LM vs. HM) or the 3 actual corresponding prosthetic feet for their group. Once randomized to PFE or actual feet, the order in which the different modes and actual feet will be tested will also be randomized; participants will be blinded to all PFE modes and actual foot conditions until the completion of the study. At visit 3 they will be tested under the other condition (e.g., if randomized to PFE testing during Visit 2, the participant would undergo testing with the corresponding actual feet during Visit 3).

The research prosthetist will fit participants with the assigned prosthetic feet (PFE or actual feet); participants will use their own prosthetic socket, interface and prosthetic suspension system. Participants will be asked to walk at their chosen comfortable speed on the treadmill while using the first randomly assigned PFE mode or actual foot until they feel comfortable. Adjustments may be made to the hardware or software settings in order to optimize the walking performance and comfort for each participant, if needed. If participants are not able to feel confident and stable on one or more of the PFE modes or on one of the actual feet, we will stop the session. We will also give participants time to rest at any point, and at every instance between switching modes or switching between actual feet. Participants will be able to take rest breaks at any time during the testing procedures and may choose to opt out of any of the tests at any time.

Please note: Participants will be allowed to hold onto the safety bars at any time on the treadmill(s) if needed in order to keep their balance. They will also be offered the option of using additional supports (e.g., gait belt, overhead safety harness) while walking on the treadmill(s) throughout the study.

When ready, all participants will be asked to walk on the treadmill for up to a minute at each of their previously-selected walking speeds: slow, comfortable, and fast. Participants will be asked to repeat these walking tasks with the second and third randomized PFE mode or actual foot, when ready. Study staff will set the PFE to the subsequent modes or the prosthetist will fit the subsequent feet.

**Group ‘HM’** (high mobility): participants will then be asked to walk again for up to a minute at their selected comfortable walking speed, this time with the treadmill inclined up to 12% grade ( $\sim 7^\circ$ ) (similar to going up a moderate to steep hill). This inclination is the maximum amount of the treadmill, and is less steep than what has been commonly used for people with lower limb amputations in previous studies. We will stop the amount of inclination before 12% grade or adjust their walking speed, if needed. Next they will be asked to stand then walk, at a comfortable walking speed, on cross slopes on each side of up to 8.5% grade ( $\sim 5^\circ$ ) for up to a minute. This cross-slope inclination has been used in previous studies with this patient population. Finally, participants may be asked to walk at a comfortable walking speed on an uneven ground treadmill for up to one minute (Pro Slat Treadmill, Woodway, Waukesha, WI). For this treadmill, low-height rock holds resembling uneven ground have been fixed to the treadmill slats to present a challenging walking surface. This uneven treadmill surface is similar to conditions used previously to simulate walking in real-world uneven terrain conditions, including in people who have lower limb amputation. Participants will be offered a break prior to walking in each condition.

**Group ‘LM’** (low mobility): participants will then be asked to walk again for up to a minute at their selected comfortable walking speed this time with the treadmill inclined up to 8.5% grade ( $\sim 5^\circ$ ) (based on the Americans with Disabilities Act (ADA) compliant ramp inclination angle). This inclination has been commonly used for people with lower mobility and lower limb amputations in previous studies, based on ADA regulations. We will stop the amount of inclination before 8.5% grade or adjust their walking speed, if needed. Next, they will stand then walk on the treadmill with cross slopes on each side of up to 5% grade ( $\sim 3^\circ$ ), and finally they will be offered the *option* of using the uneven ground treadmill for up to one minute.

When ready, participants will be asked to repeat these activities (e.g., inclined walking, cross slopes, uneven ground) with the second and third randomized PFE modes or actual feet. Between activities, participants will be given the opportunity to rest for as long as needed. During this time, they will be asked to complete a survey that includes questions about their preference, perceived stability, perceived foot stiffness, satisfaction and perceived mobility with the PFE modes or actual feet that they just walked with. These questions will occur following each activity as they complete it, or following all activities for items that refer to overall impressions about the foot that they just walked with.

Furthermore, during these visits biomechanical data may be collected using one of the following procedures: a 16-camera motion capture system (Vicon Motion Systems Ltd., Oxford, UK) to collect optical marker position data, or a set of inertial measurement units (IMUs; XSens, Movella Inc., Henderson, NV, USA) to collect acceleration data, which can be used to calculate positional data. If using the motion capture system, up to eighty reflective markers will be placed on anatomical locations (e.g., arms, legs, torso) and corresponding measurements will be taken (e.g., leg length, ankle width) according to the Vicon Full Body Plug-In Gait method. As is standard for gait biomechanical data collection, the infrared motion capture cameras will collect marker coordinate data during walking. If using the IMU system, up to twenty-five IMUs will be placed on anatomical locations (e.g., arms, legs, torso). These IMUs are commonly used, self-contained units that would be placed on participants in the same way as the reflective markers. No data will be shared with either Vicon Motion Systems Ltd. or Movella Inc. Embedded force platforms may also be used to collect synchronized ground reaction force data. The participants will be allowed to rest as much as needed between or during study activities. Dynamic stability with the foot conditions will be quantified during all walking activities from optical marker position data or IMU-based position data. The margins of stability (MOS), a commonly used biomechanical measure to assess dynamic stability in people with LLA, supposes that stable gait requires the center of mass (COM) to be controlled relative to the base of support (BOS), and the likelihood that the COM will successfully pass the leading foot can be assessed in the coronal and sagittal planes. Prosthetic foot stiffness properties in the sagittal and coronal planes may affect the COM velocity and BOS during prosthetic stance phase, especially in the presence of terrain challenges (e.g., cross-slopes and uneven treadmill), thus impacting the anterior-posterior and medial-lateral MOS. Minimum MOS in the coronal plane will be calculated based on the medial-lateral distance between the lateral border of the base of support (e.g., marker on 5th metatarsal head of the lead foot) and the vertical projection of the extrapolated COM. This technique is a modification of the original strategy proposed by Hof, et al. to define BOS based on optical markers or IMUs instead of center of pressure data, but it has a successful precedence in people with LLA under similar circumstances (e.g., variable terrains without force plates for center of pressure calculations). Similarly, anterior-posterior MOS will be calculated based on the vertical projection of the extrapolated COM relative to the posterior border of the BOS (e.g., heel marker), in accordance with published techniques in people with LLA. In calculating MOS, we will exclude strides in which participants hands are in contact with the handrail (as this would confound MOS calculations). Additionally, we will quantify handrail touches.

Once the data collection is completed, the prosthetist will refit participants' prescribed prosthetic foot. The next study visit will be scheduled and a reminder slip will be given to the participant.

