**Physical risk management:** These risks will be minimized by providing frequent rest breaks during study sessions, providing prosthetic foot acclimation periods during study sessions, fitting participants with commonly-prescribed commercially available prosthetic feet that are specific to their mobility level (low or high), conducting walking tests at participants’ self-selected speeds, and having experienced certified prosthetists conduct all prosthetic fittings. Since participants will have a chance to wear each of the commercially available feet for at least an hour in the laboratory setting with an optimized alignment, we do not expect any problems to arise during the one week at home portions of the study. However, if a participant becomes uncomfortable with the study foot for any reason during the course of the study, they will be provided the opportunity to meet with our study prosthetist who will assess the study foot and alignment and make adjustments as necessary. If not feasible to visit the study prosthetist, the study prosthetist can recommend that the participant see their own, or a local prosthetist, for the alignment assessment and change. A note will be made by the study prosthetist to document this necessity. If a participant is not comfortable wearing any of the study prosthetic feet, they can opt out and we will replace the study foot with their originally prescribed prosthetic foot and study participation can be terminated as per participant request at any time.

To minimize the risks of falls or injury, the treadmills are equipped with safety handrails, and emergency stop capabilities. Participants will also be offered the option to be fit with additional supports (e.g., safety harness that is attached to the ceiling of the lab or a gait belt) while performing walking tests on the treadmill(s) while using the prosthetic foot emulator or the commercially available study feet. If a participant declines to be fitted with the extra safety equipment but appears unsteady or experiences a fall, we will request that they wear it if they wish to continue in the study. During the balance tests, two study personnel will also be present and stay close to the participant to ensure safety during these activities. Participants will also be able to skip any or all of the performance-based clinical tests should they not feel comfortable completing them. This will not disqualify them from participating in the rest of the study.

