## **2.6 Data Analysis**

### Statistical Analysis

For both H1.1 and H1.2 (see Objectives section, 1.0 above for hypotheses details), linear mixed effects regression will be used to assess the association between Perceived Stability score, MOS, ABC, NBWT, or FSST (the dependent variables) and prosthetic foot (the independent fixed effect) with random effects for study participant. For H2.1 linear mixed effects regression will be used to test for correlation between Perceived Stability score for the emulated foot (the independent fixed effect) and follow-up Perceived Stability score for the corresponding actual foot (the dependent variable) with study participant as a random effect. For H2.2, similar models will be used to test for associations between the Perceived Stability score in the emulated foot (the independent fixed effect) and follow-up ABC, NBWT or FSST in the actual foot (the dependent variable). For H3.1 and H3.2, linear mixed effects regression will be carried out as above with initial Perceived Stability score as the independent fixed effect and Perceived Stability score, ABC, NBWT or FSST as the dependent variables with participant as the random effect. Linear mixed effects regression provides a more flexible approach to analyze repeated measures data compared to the traditional repeat measures models, with fewer model assumptions and the ability to incorporate data from participants who do not complete the study. These models account for non-independent data due to within-participant repeated measures by estimating separate between- and within-participant errors. For all models, mean and standard errors of the outcomes for each prosthetic foot and pair-wise mean differences and 95% confidence intervals (CI) across the three feet will be estimated and tested for significance.

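### Perceived Stability is rated only after an activity is completed, but sessions stop when a foot feels unstable, so the Aim 1 contrasts in that score are pulled toward zero by an unknown amount

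*Protocol*

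**What the plan says.** Section 2.5, Visit 2, states the stop rule for a participant who does not feel "confident and stable on one or more of the PFE modes or on one of the actual feet, we will stop the session". Visit 3 repeats the Visit 2 procedures with the other equipment, so the rule applies there too. Participants also "may choose to opt out of any of the tests at any time".

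On when stability is rated, the same section says: "These questions will occur following each activity as they complete it". Items on overall impressions follow all activities. No rating is called for when a session is stopped.

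The follow-up balance tests with the study feet (FSST and NBWT among them) take place at Visits 4-6. The rule that bears on them is in Risks and Risk Management: "Participants will also be able to skip any or all of the performance-based clinical tests should they not feel comfortable completing them". Doing so does not remove the participant from the study.

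Section 2.6 fits a linear mixed model with foot as fixed effect and participant as random effect. It counts among the model's strengths "the ability to incorporate data from participants who do not complete the study". The power simulation has every participant wearing all three feet and allows only for loss of whole participants.

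**The concern.** A mixed model gives unbiased contrasts from incomplete data when, given the scores in the model, the chance of being missing does not depend on the unseen score. The stop rule works the other way. Its trigger is instability on a particular mode or foot, and the score that goes unrecorded is the participant's rating of stability on that mode or foot. The least stable foot is then represented mainly by the participants who could manage it.

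At stake is the self-reported part of H1.1 and H1.2, which ties Perceived Stability to walking on uneven ground, cross-slopes and inclines. A real difference between feet would look smaller and be harder to detect. No later analysis plan can repair this, because a rating that was not taken at the stop cannot be recovered.

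**Working it through.** **1. The plan's own power figures.** Inputs from Power Analysis: NBWT within-participant SD 2.7 ft and difference 2 ft; MOS within-participant SD 1.0 cm and differences 1 and 0.7 cm; type 1 error .01. For a 2-df test of foot with means (0, 0, d), the noncentrality is n × (2/3)d² / SD².
- NBWT, n = 40: 40 × (2/3) × 4 / 7.29 = 14.6, power 82.6% (stated 81%).
- NBWT, n = 50: 18.3, power 91.6% (stated 91%).
- MOS, 1 cm, n = 40: 26.7, power 98.8% (stated 98%).
- MOS, 0.7 cm, n = 50: 16.3, power 87.5% (stated 87%).

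The stated figures are reproduced within 2 points, with every foot observed on every participant.

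**2. The mechanism by hand.** The protocol gives no SD for Perceived Stability. The NBWT values serve here only as a scale: 2 / 2.7 = 0.74 within-participant SDs. Suppose a stop occurs when the foot-specific part of the score falls below a cut-off that removes the lowest 10% on the worst foot.
- Worst foot: the cut-off lies 1.28 SD (3.46 ft) below its mean. The mean of the scores that remain rises by 2.7 × 0.1755 / 0.90 = 0.53.
- Other feet: the same cut-off lies (3.46 + 2) / 2.7 = 2.02 SD below their mean. Their mean rises by 2.7 × 0.0516 / 0.978 = 0.14.
- Contrast: 2 − 0.53 + 0.14 ≈ 1.6 instead of 2, about 19% too small.

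**3. Simulation of the stop rule.** 400,000 participants, SDs 4.1 and 2.7, random-intercept model on observed scores with variance components held fixed. A stop loses the trigger foot and every later foot in random order. The trigger rates are assumptions. Pairwise power is at n = 48 (60 × 0.8), two-sided .01.

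| Worst-foot scores triggering a stop | Estimate (true 2.00) | Shrinkage | Pairwise power |
|---|---|---|---|
| none | 2.00 | 0% | 86% |
| 5% | 1.78 | 11% | 71% |
| 10% | 1.62 | 19% | 57% |
| 20% | 1.39 | 31% | 35% |
| 30% | 1.21 | 40% | 20% |

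Losing the whole session gives the same estimates. When loss depends only on the participant's general ability, or is unrelated to the score, the estimate stays at 2.00-2.01.

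**4. On a Perceived Stability scale.** With assumed SDs and a true contrast of 0.70, stops triggered by 8-27% of worst-foot ratings gave 0.61 to 0.49: (0.70 − 0.61) / 0.70 = 13% and (0.70 − 0.49) / 0.70 = 30%. Including one rating taken at the stop brought the estimate back to 0.70, because the loss of later feet then depends only on ratings that the model contains.

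**5. Aims 2 and 3.** Initial Perceived Stability is the predictor there. With an assumed slope of 0.60 and stops on low initial ratings, the slope stayed at 0.60. In a separate run with slope 0.50, the slope was again unchanged, while the raw correlation fell from 0.46 to 0.40 at 10% loss.

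**6. NBWT.** If skipping follows a low score on the foot, with 6-10% skipping at random among low scorers on the worst foot, a true 1.92 ft became 1.82-1.85 ft: 0.07 / 1.92 = 4% to 0.10 / 1.92 = 5%. A sharp threshold gave 7% at 5% loss and 11% at 10%.

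**The case against.** The strongest case is that stops may be rare. Visit 1 has participants try the emulator modes before randomisation, fittings can be adjusted, handrails and harness are available, and incline and speed can be reduced. Ratings for activities finished before a stop are kept. The protocol also allows a return visit to recapture missing data. All of this stands, and it lowers the size. It does not remove the problem: the return visit is discretionary, and the participant would walk on the same foot under the same stop rule.

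A second objection is that handling of missing data belongs in an analysis plan that is not shown. That holds for imputation and sensitivity analyses. It does not hold for a rating that is never collected.

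Three stronger readings are tempting and are not supported:
- A reader might infer that the Aim 2 and 3 slopes are biased toward zero. The stop rule selects on the predictor, which leaves a correctly specified slope unchanged.
- A reader might infer that NBWT and FSST are missing by design because of the foot. The stop rule is written for Visits 1-3, while these tests with study feet come at Visits 4-6. The skip rule speaks of comfort and names no foot. If it reflects general ability, foot contrasts are not biased.
- A reader might take the exclusion of those who "are unable to use more than one of the test feet for any reason" as admitting people unstable on one foot. Its own example is a residual limb too long for the foot, which is a matter of physical fit.

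**Conclusion.** The concern holds for the Aim 1 Perceived Stability contrasts. Their direction is toward zero; their size cannot be fixed from the protocol, which gives neither a stop rate nor an SD for that score. The 13-30% range rests on assumed SDs and on 8-27% of worst-foot ratings triggering a stop; rarer stops give less. The only nearby figure, a dropout rate below 5% in the current emulator study, counts people leaving a study, not stopped sessions.

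The verdict assumes that Aim 1 uses ratings from the Visit 2-3 sessions with actual feet. The wording of H1.1 and H1.2 suggests this, since the walking conditions are only optionally repeated at follow-up. Stops in the emulator session do not enter the Aim 1 contrasts. For NBWT and FSST the bias is conditional on foot-driven skipping, and for the Aim 2 and 3 slopes the stop rule causes none.

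**What to change.** Leave the safety rules unchanged and add the following.

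1. Whenever a session is stopped or a test declined, record the reason by foot, separating instability on that foot from general discomfort, scheduling and equipment.
2. At a stop, take the Perceived Stability rating for that foot at that moment and include it in the Aim 1 model.
3. For NBWT and FSST declined because of instability on the foot, add a sensitivity analysis, either a worst-rank score or able/unable by foot, beside the observed-data model and not in its place. Entering a declined NBWT as 0 ft and letting that version decide is not advised: in simulation it overshot, giving about −2.16 ft against a true −1.93 ft.

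The cost is one reason code, one rating and one extra model run per outcome. The rating at a stop follows a shorter walk than the others and should be flagged as such. It restores the contrast fully when the stop is triggered by the rating itself. If the trigger is instead a drop below the participant's own norm, it recovers most of the loss but may leave a residual.
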